### Randomization and blinding

All eligible AIS participants will be randomly assigned into either the manipulation techniques group and the control group with an allocation ratio of 1:1. A random number table will be generated with a computerized random number generator program. Each computer-generated random number will be matched with either group and then be sorted in ascending order, which causes the list to rearranged sequence.

After the randomization, group name will be displaced by a specific code in order to keep the blinding in the study. The random allocations will be placed in sequentially numbered, opaque, and sealed envelopes. Two sets of the envelope will be prepared, with one set for randomization at the site and another set stored in the investigator’s office for emergency unblinding. Following the initial evaluations, the numbered envelopes will be given to each participant according to the order of each participant admitted to the study.

This process will be performed by a researcher who will not be involved in the participant enrolment, allocation and assessment. There will be no permission for unblinding the outcome assessor or the participants during the study. The participant can only be informed about their group allocation upon completion of the study.

### Participant timeline

As shown in the Fig. 1 and Table 1, each participant has a face-to-face interview in screening, a total four visits to the Chinese medicine clinic, 12 times orthopaedic manipulation or sham treatment and 14 sessions of PSSE training throughout the study. Community participants who express interest in our study and agree for our telephone screening will leave their contact to project researcher. Potential participants referred from the clinics or medical centres will be screened directly. In the screening, information about the study will be explained to the participants and their parents/guardians. Both participants and their parents/guardians will then sign informed consent form voluntarily at their agreement. Eligible participants after screening will be arranged a face-to-face interview for eligibility assessment.

**Fig. 1 Fig1:**
[figure not shown]
Study flowchart

### Data management

To protect patient privacy, all research data would be handled in line with Hospital Authority and Hospital’s policy in handling, storage and destruction of participants’ medical records. They would be locked in cabinets where the department keeps the participants’ confidential information. All collected information will be input into a computer with restricted access to investigators only. Only de-identified data will be collected and removed from the premises. All information will be encrypted and only the involved investigators can have access. Password is required to access the data.

### Statistical analysis

All analyses will be conducted according to the intention-to-treat principle. Descriptive statistics will be computed for each of the analysed variables. The primary efficacy analysis will be done by comparing the two groups with respect to score of SRS-22 at baseline and at 8, 16 and 24 weeks after randomization using analysis of covariance (ANCOVA). A complete-case analysis and a linear mixed model analysis of all available data will then be done as supplementary analyses. Repeated measures ANCOVA will be used to test for group differences in the secondary outcomes, including score of TC-SAQ and ISYQOL and the measurement in spinal imaging with adjustment for relevant baseline covariates. Unauthorized treatment will also be added as a covariate in relevant ANCOVA. All statistical tests will be two-sided, and *p* < 0.05 is considered significant difference. The statistical software of SPSS 23.0 will be used for analysis. Adverse events will be categorized, and the percentage of the mild adverse events and serious adverse events will be documented. Chi-square tests will be used to examine differences in the proportion of total and categories of adverse events within each group.

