Secondary outcomes also include the change of Cobb’s angle measured by Xray at week 16, and the change of Cobb’s angle, spinal rotation and muscle volume measured by 3D ultrasound imaging before and after every manipulation. The paraspinal muscle volume will be estimated by a customized MATLAB program, which multiplies the cross-sectional area of paraspinal muscles on each image by the thickness of each image and the total number of images of the target paraspinal muscle. The lateral curvature of the spine in the coronal plane measured by Cobb’s method on X-ray radiograph is the gold standard for assessing scoliosis [33], In the study, a standing whole-spine PA radiograph will be used for measurement and evaluated before and after the 24-week study period. If the patient has double curves, the major curve will be calculated for analysis. Moreover, before and after every manipulation, Cobb’s angle, spinal rotation and muscle volume along the spine will be measured from 3D ultrasound imaging captured by Scolioscan Air. Scolioscan Air is a validated radiation-free system for scoliosis assessment by using coronal images of spine generated by a 3D ultrasound volume projection imaging method [34, 35].

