### Participants withdrawal

Participants can withdraw at any time because of personal reasons, adverse events or serious adverse events. An attempt to contact the participant will be made to ask for an explanation for incompliance or termination, and the results of the last assessment should be recorded. For participants who withdraw from the study due to adverse reactions, or treatment failure, appropriate treatment measures should be conducted immediately. Participants are free to withdraw at any time without giving a reason or punishment. All participants are encouraged to attend the follow-up assessment at 24th week for adverse event assessment for the best disease monitoring and participants’ benefit.

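### Repeated-measures ANCOVA for the secondary outcomes usually drops anyone with one missing value, against the intention-to-treat promise, and week-16 data are not sought after treatment stops

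*Protocol article*

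**What the plan says.** All points are from the protocol article.

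- **Principle (Statistical analysis):** "All analyses will be conducted according to the intention-to-treat principle".
- **Primary outcome (Outcomes; Statistical analysis):** change in SRS-22 at week 16, with the groups compared by ANCOVA. Directly after that sentence: "A complete-case analysis and a linear mixed model analysis of all available data will then be done as supplementary analyses".
- **Secondary outcomes (Statistical analysis):** "Repeated measures ANCOVA will be used to test for group differences in the secondary outcomes". The outcomes listed are TC-SAQ, ISYQOL and the spinal imaging measures. On software: "The statistical software of SPSS 23.0 will be used for analysis". Neither the SPSS procedure nor the handling of missing values is named.
- **Number of measurements (Outcomes; Interventions; Participant timeline):** questionnaires at weeks 8, 16 and 24. Before and after each of 12 sessions, Cobb's angle, spinal rotation and "muscle volume along the spine will be measured from 3D ultrasound imaging captured by Scolioscan Air".
- **Dropout (Sample size estimation):** 20% allowed for, 50 randomised.
- **After withdrawal (Participants withdrawal):** the last assessment is recorded, and "All participants are encouraged to attend the follow-up assessment at 24th week for adverse event assessment". Week 16 is not mentioned there.

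**The concern.** Intention-to-treat means analysing participants as randomised, with loss kept small or handled explicitly. Classical repeated-measures ANCOVA, as run through the SPSS general linear model procedure, needs a value in every cell of the repeated factor and discards the rest of a participant's data when one is missing. A plan that expects one in five to drop out and names this method for all secondary outcomes is likely to report on a subset selected by attendance. The all-available-data model that would avoid this is written into the same section, but its position ties it to SRS-22.

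The ultrasound outcomes are the most exposed, because they have by far the most measurement occasions. They also carry the stated secondary objective, the association between muscle volume and spinal curve around each treatment.

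The second issue is data collection. The primary endpoint falls at week 16, but the only visit the withdrawal section encourages is week 24, for safety. An analysis plan cannot recover a week-16 questionnaire that nobody requested.

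**Working it through.** **Inputs from the protocol article.** Difference 0.4, SD 0.45, power 80%, two-sided 0.05, 21 per group, 20% dropout, 50 in total (Sample size estimation; Statistical analysis). 12 sessions (Interventions). Three follow-up visits (Participant timeline).

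**Assumptions, not in the article.** Chance q of missing any one session or visit: 2%, 5% or 10%, independent. Correlation ρ between week-8 and week-16 SRS-22: 0.5 to 0.7.

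**1. The plan's own figure.** Normal approximation: n = 2(1.960 + 0.842)² × 0.45² / 0.4² = 19.9, so 20 per group. The exact noncentral t calculation gives 21 per group (power 80.3%), which matches. After the planned dropout, 50 × (1 − 0.20) = 40 participants remain.

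**2. Complete cases under listwise deletion.** Expected number = 40 × (1 − q)^k, with k the number of occasions that can be missed.

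| q | 3 questionnaire visits | 12 ultrasound sessions |
|---|---|---|
| 2% | 40 × 0.98³ = 37.6 | 40 × 0.98¹² = 31.4 |
| 5% | 40 × 0.95³ = 34.3 | 40 × 0.95¹² = 21.6 |
| 10% | 40 × 0.90³ = 29.2 | 40 × 0.90¹² = 11.3 |

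The session column treats the two scans of a session as missed together. If each of the 24 scans could be missed separately, the same formula with k = 24 gives about 25, 12 and 3.

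**3. Bias in the week-16 contrast when withdrawn participants are not followed.** Suppose there is no true effect, SD is 0.45, the fraction d of each arm with the lowest week-8 scores drops out, and there is no covariate adjustment. The mean week-16 score of those who stay is then raised by ρ × 0.45 × φ(z_d)/(1 − d), where φ is the standard normal density and z_d the normal quantile at d. The factor φ(z_d)/(1 − d) is 0.195 at 10%, 0.350 at 20% and 0.497 at 30%.

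| Dropout, arm A vs B | ρ = 0.5 | ρ = 0.7 |
|---|---|---|
| 20% vs 20% | 0 | 0 |
| 30% vs 10% | (0.497 − 0.195) × 0.45 × 0.5 = 0.07 | (0.497 − 0.195) × 0.45 × 0.7 = 0.10 |
| 20% vs 0% | 0.350 × 0.45 × 0.5 = 0.08 | 0.350 × 0.45 × 0.7 = 0.11 |

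A simulation gave the same values to two decimals. The unequal cases run from 0.068/0.4 = 17% to 0.110/0.4 = 28% of the target difference.

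In this scenario dropout depends only on the observed week-8 score, so a mixed model that includes week 8 would correct for it. Dropout that depends on the unobserved week-16 state would not be corrected, and collecting the week-16 value is the remedy there.

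**The case against.** - **Listwise deletion is inferred.** The article names no SPSS procedure, and repeated-measures ANCOVA can be run after imputation. This stands as a caution: deletion is a property of the usual procedure, not something the article states. But the article names a method whose ordinary form conflicts with its own principle and attaches no remedy to these outcomes.
- **The primary analysis.** A reader might infer that the week-16 ANCOVA is itself a complete-case analysis, so that every analysis in the trial is a selected subset. The article does not support that. It lists complete-case analysis separately as supplementary, which suggests the ANCOVA is meant to be something else, and it already plans a mixed model for SRS-22. How the ANCOVA treats missing week-16 values is unstated and may sit in a fuller document.
- **The ultrasound loss.** A reader might infer that these analyses would lose most of their sample. That depends on the missed-session rate: 31 of 40 remain at 2% and 22 of 40 at 5%, and only the 10% case leaves a clear minority. The article does not say that the whole series enters one model. Session-level changes or summaries would also fit its wording, and missed sessions might be rebooked.
- **Retention.** A reader might infer that withdrawn participants can yield no efficacy data. In fact the last assessment is recorded, and questionnaires are collected at every follow-up visit, so someone who attends week 24 may complete SRS-22 then. What remains is that week 16 is not sought.
- **Bias.** Outcome-related loss that shifts one arm's mean does not by itself bias the contrast. With equal loss of the same kind in both arms the bias is about 0. Differential loss is plausible, since only one arm receives the forceful thrust and withdrawal for adverse reactions or treatment failure is foreseen, but the article gives no figures for it.

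**Conclusion.** The point holds for the secondary outcomes and, in a limited form, for week-16 follow-up. The method named for TC-SAQ, ISYQOL and repeated imaging fits poorly with the intention-to-treat promise when 20% dropout is planned. The likely cost is modest for the questionnaires (about 29 to 38 of 40 complete) and potentially large for the ultrasound series (about 11 to 31 of 40). These figures rest on independent misses at 2% to 10%, on the usual listwise procedure, and for ultrasound on the full series being the repeated factor.

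The withdrawal section does not secure the primary endpoint from those who stop treatment. The consequence is conditional: 0.07 to 0.11 SRS-22 points if loss differs between arms as illustrated, and about 0 if it is the same. The article does not show that the primary analysis is complete-case. It is worth changing because the better method is already in the plan.

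**What to change.** 1. **Secondary outcomes.** Use the planned linear mixed model for TC-SAQ, ISYQOL and the repeated ultrasound measures: baseline as covariate, with group, visit (or session) and group by visit (or session). Keep repeated-measures ANCOVA as a sensitivity analysis. For the ultrasound series choose a simple covariance structure in advance: an unstructured matrix for 24 scans has 24 × 25 / 2 = 300 parameters, too many for about 40 to 50 participants.
2. **Primary outcome.** Keep the planned mixed model for the week-16 contrast, and add one sentence on how the ANCOVA handles missing week-16 values, so that it does not simply duplicate the supplementary complete-case analysis.
3. **Follow-up.** In the withdrawal section, separate stopping treatment from withdrawing consent. Ask everyone who stops treatment but keeps consent to complete the week-16 SRS-22, remotely if needed, in addition to the week-24 safety visit.

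**Cost.** Analysis wording, no new software (a mixed model in SPSS is already planned), and staff time for a few questionnaires. The mixed model still assumes that missingness is explained by the observed data, which is why item 3 is needed as well as item 1.

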### Objectives and hypothesis

The primary objective of the study is to evaluate the clinical efficacy and safety of the OMT-LSLR in the treatment of AIS. The secondary objective is to determine the association between the change in the muscle volume and the spinal curve before and after every treatment. The hypothesise is that the OMT-LSLR is effective for the treatment of Adolescent Idiopathic Scoliosis which will balance the musculoskeletal difference between both sides of the patient’s back.

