## Methods/design

### Study design

This study is a prospective trial in participants with AIS and is a participant-and-assessor-blinded randomized controlled trial with the treatment duration of 16 weeks and post-treatment follow-up period of 8 week. Fifty eligible participants will be randomly divided into two groups: the manipulation techniques group and the control group. The allocation ratio will be 1:1. participants in the former group will receive both OMT-LSLR and PSSE, whereas those in the latter group will receive sham manipulation technique, which is similar to OMT-LSLR without any therapeutic effect, and PSSE.

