### Sample size estimation

PASS 12.0 was used for the sample size calculation. The Scoliosis Research Society-22 (SRS-22) questionnaire score was chosen as the primary outcome indicator. The minimal clinically important difference of SRS-22 ranges from 0.4–0.7 [41]. The standard deviation was estimated to be 0.45 from previous studies about non-operative treatments in AIS patients [42]. To detect a clinically meaningful different of 0.4 in SRS-22, with 80% power at the 0.05 significance level and an assumed standard deviation of 0.45, 21 cases in each group are required. Allowing for a dropout rate of 20%, a total of 50 participants will be recruited with 25 participants for each group.

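### The only safety test in the protocol is worded as a comparison within each arm, so as written it does not compare manipulation with sham

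*Protocol article*

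**What the plan says.** Under Objectives and hypothesis, the protocol article puts safety beside efficacy: "The primary objective of the study is to evaluate the clinical efficacy and safety of the OMT-LSLR in the treatment of AIS".

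The Statistical analysis section has two sentences on adverse events. The first is descriptive: events will be categorised and "the percentage of the mild adverse events and serious adverse events will be documented". The second is the only test: "Chi-square tests will be used to examine differences in the proportion of total and categories of adverse events within each group".

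For efficacy, the same section names the contrast directly: "The primary efficacy analysis will be done by comparing the two groups with respect to score of SRS-22". The sentence on secondary outcomes likewise speaks of differences between groups.

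The design supports a between-arm safety comparison. The Study design section states "The allocation ratio will be 1:1", with sham manipulation plus exercise as the control, and the Sample size estimation section states that "a total of 50 participants will be recruited with 25 participants for each group".

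**The concern.** A test confined to one arm has no comparator. It can ask whether one category of event is more frequent than another in that arm. It cannot ask whether manipulation leads to more events than sham.

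This matters for three reasons. Safety is half of the primary objective and is in the title. The sham control allows a controlled estimate of harm. And both arms do scoliosis-specific exercises, in supervised sessions and daily at home, so events such as muscle soreness may arise in either arm for reasons unrelated to the manipulation. A count from the manipulation arm alone mixes the two sources, and the difference between arms is what separates them.

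The point does not rest on an omission that an unseen analysis plan could fill. The article states a contrast, and as worded it is not the one that the objective needs.

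**Working it through.** **1. Is a between-arm safety test stated anywhere?** The relevant sections, side by side:

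| Section | What it covers on safety | Between-arm test? |
|---|---|---|
| Objectives and hypothesis | Safety is in the primary objective | No test given |
| Safety | Background risk from earlier manual-therapy literature | No |
| Participant timeline | Recording of events at visits; daily record of side effects | No |
| Participants withdrawal | Week-24 attendance for adverse-event assessment | No |
| Statistical analysis, descriptive sentence | Percentages of mild and serious events | No |
| Statistical analysis, test sentence | Chi-square, worded as within each arm | Not as written |
| Statistical analysis, efficacy sentences | Two groups compared | Yes, but for SRS-22 and secondary outcomes only |

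The safety test is the only analysis in that section not worded as a comparison of the groups.

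**2. What does the right contrast deliver?** The protocol states no adverse-event rate and no figure for the safety test, so there is nothing of its own to reproduce. For illustration, assume that 10 of 25 manipulation participants and 2 of 25 sham participants have at least one event. The 25 per arm is from Sample size estimation; the counts are assumed.

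- Risk difference: 10/25 − 2/25 = 0.40 − 0.08 = 0.32.
- Standard error: √(0.40 × 0.60/25 + 0.08 × 0.92/25) = √(0.009600 + 0.002944) = 0.112.
- Approximate 95% CI: 0.32 ± 1.96 × 0.112 = 0.10 to 0.54.
- Pearson chi-square between arms: 50 × (10 × 23 − 2 × 15)² / (25 × 25 × 12 × 38) = 2,000,000 / 285,000 = 7.02, p = 0.008. Fisher's exact p = 0.018.

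**3. What would a within-arm test deliver on the same data?** The protocol states no within-arm null hypothesis. If an even split of affected and unaffected participants is tried, only to see how such a test behaves:

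- Manipulation, 10 against 15: (10 − 12.5)²/12.5 + (15 − 12.5)²/12.5 = 1.00, p = 0.32.
- Sham, 2 against 23: (2 − 12.5)²/12.5 + (23 − 12.5)²/12.5 = 17.64, p < 0.0001.

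The significant result falls in the arm with fewer events. This does not measure what the plan loses, because the null is not the protocol's. It shows only that a p-value from within one arm carries no information about the difference between arms.

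**4. Is chi-square itself a fault at 25 per arm?** Exact enumeration of all 2 × 2 tables at 25 per arm, at the nominal two-sided 5% level ("All statistical tests will be two-sided"), over assumed event rates:

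| True rate in both arms | Size, uncorrected chi-square | Size, Fisher |
|---|---|---|
| 5% | 2.0% | 0.1% |
| 10% | 4.9% | 0.9% |
| 20% | 5.5% | 2.2% |
| 50% | 6.5% | 3.3% |

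| True rates, manipulation vs sham | Power, chi-square | Power, Fisher |
|---|---|---|
| 10% vs 2% | 15% | 2% |
| 20% vs 4% | 44% | 23% |
| 40% vs 8% | 81% | 68% |

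The 6.5% is the largest chi-square size found over rates from 1% to 50%. The two tests can disagree in sparse tables (4 against 0: chi-square p = 0.037, Fisher p = 0.110). The error rate of the chi-square nevertheless stays near or below nominal, and Fisher's test gives up power to detect harm.

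**The case against.** The strongest defence is that the sentence is loose English for comparing, across the arms, the proportion found in each. The reference to total adverse events favours this: inside a single arm the total proportion has no second proportion to differ from, so the literal reading yields no coherent test for it. This stands as an account of what the authors may have meant. It does not rescue the text, because the reader must replace the stated contrast with another, and the same section words its efficacy contrasts clearly.

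A second defence is that events will be recorded and percentages documented, so an imbalance would be visible if tabulated by arm. This also stands. A reader might infer that the plan can never compare the arms or cannot show excess harm, and the documents do not support either. What is missing is a clearly stated between-arm comparison with an estimate and its uncertainty.

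A reader might also infer that chi-square is unreliable at this sample size and that Fisher's exact test must replace it. That is not supported. The protocol gives no event rate, so sparse tables are plausible for serious events and single categories but not established for events overall. The exact sizes above do not show a test that breaks down, and Fisher's test has a real cost in power. How sparse tables are handled can be left to the analysis plan.

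**Conclusion.** The point holds as a defect of wording in the contrast, at should-fix level. Followed literally, the plan does not test manipulation against sham on safety, which is part of its primary objective, and no other section supplies that test. This rests on the text alone and needs no assumption about event rates.

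The practical size cannot be fixed from the documents, because no adverse-event rate is given; the 32-point difference is an assumed example. The primary SRS-22 analysis, the sample size (set for SRS-22 "with 80% power at the 0.05 significance level") and the data collection are unaffected. The choice of chi-square is not part of the finding.

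**What to change.** Replace the test sentence in the Statistical analysis section with wording such as: the number of participants with at least one adverse event (total, by category, and serious) will be compared between the manipulation and sham groups, and the risk difference will be reported with its 95% confidence interval.

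Counting participants, rather than events, keeps the observations independent when one participant reports several events. The test for sparse tables can be named in the analysis plan.

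The cost is one sentence, with no change to recruitment, visits, data collection or sample size. It should be made before unblinding, so that the safety contrast is not chosen after the data are seen.

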**Discussion:**

The results of this study will establish comprehensive clinical evidence about the efficacy and safety of the Orthopaedic Manipulation Techniques of the Lin School of Lingnan Region in the Treatment of Adolescent Idiopathic Scoliosis. One of the characteristics of this trial is that it is a participant-and-assessor-blinded randomized controlled clinical trial with sham manipulation. The study would also apply three-dimensional (3D) ultrasound technology to investigate the relationship between the change of the muscle volume and the spinal curve.

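### Safety is part of the primary objective, but the only safety inference named is a p < 0.05 chi-square test in a trial of 50 sized on SRS-22; estimates with confidence limits would serve the objective better at almost no cost

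*Protocol article*

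**What the plan says.** Under Objectives and hypothesis: "The primary objective of the study is to evaluate the clinical efficacy and safety of the OMT-LSLR in the treatment of AIS".

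In the Discussion part of the abstract: "The results of this study will establish comprehensive clinical evidence about the efficacy and safety of the Orthopaedic Manipulation Techniques".

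Under Statistical analysis, adverse events are to be categorised and "the percentage of the mild adverse events and serious adverse events will be documented". The test follows: "Chi-square tests will be used to examine differences in the proportion of total and categories of adverse events"; the sentence ends by placing this comparison inside each group. The general decision rule is "All statistical tests will be two-sided, and *p* < 0.05 is considered significant difference".

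Under Sample size estimation, the only target is the questionnaire: "To detect a clinically meaningful different of 0.4 in SRS-22, with 80% power at the 0.05 significance level". No adverse-event rate, difference or bound enters the calculation. The Safety section describes expected harms in words only: minor events are short-lived (a statement about adults) and major events are very uncommon.

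**The concern.** A significance test asks whether the data contradict equal event rates. A safety objective asks how large an excess of harm the data can rule out. In a small trial the two questions can have very different answers: a test can be non-significant while the data remain compatible with a sizeable excess.

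The protocol names only the first kind of inference for the safety half of its primary objective, and the abstract describes the expected result in strong terms. The treatment applies a sudden force to the spine of participants aged 10 to 18. A report stating only percentages and a non-significant p-value could lead readers to infer reassurance that 25 treated participants cannot give.

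The point does not depend on two neighbouring issues: the phrase about testing inside each group, and whether chi-square suits sparse counts. A correctly specified between-arm exact test would leave it in place.

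**Working it through.** **Inputs from the protocol.** 25 per arm, 1:1, two-sided 0.05, 20% dropout (25 × 0.8 = 20 per arm); SRS-22 difference 0.4, SD 0.45, power 80%, 21 per group. **Assumed:** participant-level event rates, shown as a range because the protocol gives none.

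**1. The plan's own figure.** The normal approximation gives n = 2(1.960 + 0.842)² × 0.45² / 0.4² = 19.9, so 20 per group. With the noncentral t distribution, power is 0.782 at 20 and 0.8025 at 21. The stated 21 reproduces, but it concerns SRS-22 only; there is no safety calculation to reproduce.

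**2. Power of a between-arm test.** For counts i (sham, rate p₁) and j (manipulation, rate p₂), power is the sum of Bin(i; n, p₁) × Bin(j; n, p₂) over all pairs with j > i and two-sided p < 0.05. The uncorrected Pearson statistic is z = [(j − i)/n] / √[p̄(1 − p̄) × 2/n], with p̄ = (i + j)/(2n).

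| Sham vs manipulation | Pearson, n = 25 | Fisher, n = 25 | Pearson, n = 20 | Fisher, n = 20 |
|---|---|---|---|---|
| 10% vs 20% | 0.172 | 0.085 | 0.136 | 0.072 |
| 10% vs 30% | 0.450 | 0.305 | 0.357 | 0.242 |
| 20% vs 40% | 0.351 | 0.231 | 0.291 | 0.192 |
| 5% vs 25% | 0.555 | 0.370 | 0.444 | 0.299 |
| 20% vs 50% | 0.638 | 0.510 | 0.531 | 0.409 |
| 10% vs 40% | 0.734 | 0.591 | 0.623 | 0.492 |

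Hand check for 10% vs 30% at n = 25: (0.20 − 1.96 × √(2 × 0.2 × 0.8/25)) / √((0.09 + 0.21)/25) = (0.200 − 0.222)/0.110 = −0.20, so power is about 0.42 by normal approximation, close to the exact 0.450. By the same approximation, 80% power would need 62 per arm for 10% vs 30% and 199 per arm for 10% vs 20%.

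**3. Serious events.** With none in the sham arm, the smallest manipulation count that reaches p < 0.05 is:
- Pearson: 4 of 25. For 4 vs 0, z = 0.16/√(0.08 × 0.92 × 0.08) = 2.09. For 3 vs 0, z = 0.12/√(0.06 × 0.94 × 0.08) = 1.79, which is not significant.
- Fisher: 6 of 25. For 5 vs 0, p = 2 × 53,130/2,118,760 = 0.0502. For 6 vs 0, p = 2 × 177,100/15,890,700 = 0.022.

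If serious events are as uncommon as the Safety section expects, non-significance for that category is therefore close to certain. This does not carry over to total or minor events.

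**4. What zero events would show.** Solving (1 − p)²⁵ = 0.05 gives p = 1 − 0.05^(1/25) = 0.113 (one-sided 95%). With 0.025 in place of 0.05, p = 0.137 (two-sided 95%).

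**5. What an interval would show.** Take 2 of 25 affected in each arm. The Wilson limits for 0.08 are 0.022 and 0.250. Newcombe's score interval for the difference is 0 ± √(0.058² + 0.170²), about −18 to +18 points. A bare p-value conveys none of this.

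**The case against.** The strongest reply is that the protocol never turns non-significance into a safety claim. It gives no decision rule for safety and reports percentages alongside the test. The stated aim is to evaluate safety, and the abstract promises evidence about safety, not proof of it. All of that stands. A reader might infer that the plan treats p ≥ 0.05 as proof of safety, or that it undertakes to prove the treatment safe; the text supports neither.

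Nor does the text support saying that the trial would usually miss any relevant harm. The protocol defines no relevant excess, so every power figure rests on assumed rates. Chi-square at a full 25 per arm has better than even power for 5% vs 25% and for the 30-point excesses shown. The 80% power target belongs to SRS-22 and sets no standard for detecting harm.

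Two further replies are fair. Margins and confidence intervals may be left to an analysis plan that is not shown, so their absence alone is not the point. Sizing a trial of 50 on its efficacy outcome is also ordinary practice, and the 11.3% bound would hold under any analysis of 25 participants.

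What remains is that the objective, the strong word in the abstract, the named test and the basis of the sample size are all in print and fit together poorly. An unseen plan could add intervals, but it could not make 25 treated participants establish much about uncommon harms.

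**Conclusion.** The point holds as a cheap improvement, not as an error that undermines the trial. The one inferential safety method named suits the safety half of the primary objective poorly, and the abstract's verb is stronger than 25 treated participants can support.

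Under the assumed rates, a between-arm Pearson test at 25 per arm has about 17% power for 20% vs 10% and 45% for 30% vs 10% (Fisher 9% and 31%). It reaches 56% for 25% vs 5% and 73% for 40% vs 10% (Fisher 37% and 59%). Low power is thus a matter of small and moderate excesses, not of every excess. The zero-event bounds of 11.3% and 13.7% need no assumed rate, only complete follow-up of 25 treated participants and independent outcomes.

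**What to change.** In Statistical analysis, make estimation the main safety analysis. For any adverse event, each category and serious adverse events, report:

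- the number of participants affected in each arm;
- the between-arm risk difference with an exact or score 95% confidence interval;
- for serious events in the manipulation arm, the exact upper 95% bound, even if none occur, stating whether it is one- or two-sided.

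Add a sentence that p ≥ 0.05 will not be taken as evidence of safety. Any test that is kept should be secondary.

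In the abstract's Discussion, separate safety from efficacy and describe the trial as providing preliminary safety estimates. It could add that, with no serious events in 25 treated participants, a risk of up to about 11% (one-sided 95%) cannot be excluded.

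The cost is a few sentences and some intervals from adverse-event data already to be collected, with no extra participants, visits or procedures. The price is a less favourable stated safety conclusion.
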